## Abstract

**Background:**

Depression is highly prevalent within individuals diagnosed with schizophrenia, and is associated with an increased risk of suicide. There are no current evidence based treatments for low mood within this group. The specific targeting of co-morbid conditions within complex mental health problems lends itself to the development of short-term structured interventions which are relatively easy to disseminate within health services. A brief cognitive intervention based on a competitive memory theory of depression, is being evaluated in terms of its effectiveness in reducing depression within this group.

**Methods/Design:**

This is a single blind, intention-to-treat, multi-site, randomized controlled trial comparing Positive Memory Training plus Treatment as Usual with Treatment as Usual alone. Participants will be recruited from two NHS Trusts in Southern England. In order to be eligible, participants must have a DSM-V diagnosis of schizophrenia or schizo-affective disorder and exhibit at least a mild level of depression. Following baseline assessment eligible participants will be randomly allocated to either the Positive Memory Training plus Treatment as Usual group or the Treatment as Usual group. Outcome will be assessed at the end of treatment (3-months) and at 6-month and 9-month post randomization by assessors blind to group allocation. The primary outcome will be levels of depression and secondary outcomes will be severity of psychotic symptoms and cost-effectiveness. Semi-structured interviews will be conducted with all participants who are allocated to the treatment group so as to explore the acceptability of the intervention.

**Discussion:**

Cognitive behaviour therapy is recommended for individuals diagnosed with schizophrenia. However, the number of sessions and length of training required to deliver this intervention has caused a limit in availability. The current trial will evaluate a short-term structured protocol which targets a co-morbid condition often considered of primary importance by service users. If successful the intervention will be an important addition to current initiatives aimed at increasing access to psychological therapies for people diagnosed with severe mental health problems.

**Trial registration:**

Current Controlled Trials. ISRCTN99485756. Registered 13 March 2014.

## Background

The annual cost of the treatment of schizophrenia within the UK has been estimated at over £2billion, which is approximately 3% of the NHS budget [1]. Consequently, the development of cost-effective interventions for schizophrenia is a priority. Current UK government guidelines recommend psychological therapy for the treatment of schizophrenia. Specifically, cognitive-behavioural therapy (CBT), in the form of at least 16 sessions over a minimum of 6 months, is advised [2]. Most current evidence-based CBT protocols for the treatment of schizophrenia are designed to be generic and flexible. This enables the clinician to work with the wide range of complex presentations, including high levels of co-morbidity, that are associated with a diagnosis of schizophrenia. However, it is often a co-morbid diagnosis such as posttraumatic stress disorder or depression that both the clinician and patient consider the priority for intervention.

About half of the people diagnosed with schizophrenia also suffer from depression [3]. This co-morbid condition is associated with particularly high levels of health care use, and a suicide rate of 5% [4]. The effectiveness of anti-depressants is equivocal [5] in this group. To date, there have been no clinical trials to evaluate the effectiveness of a psychological intervention which targets the treatment of depression within these co-morbid patients. The evidence base that supports psychological interventions for depression, such as CBT [6], behavioural activation [7] and mindfulness [8] is derived from trials which have excluded individuals diagnosed with schizophrenia. There is some evidence that 6 to 12 months of generic CBT targeting the symptoms of schizophrenia does achieve a small to moderate effect on mood [9]. However, the training that is required for NHS clinicians to provide this generic intervention is lengthy, expensive, and limited to a relatively small number of specialists. Consequently, there is limited access to CBT for people diagnosed with schizophrenia. The targeting of conditions co-morbid with schizophrenia, such as depression, lends itself to the development of short-term structured psychological interventions, which can be packaged into the form of a manualised protocol. These interventions are relatively easy to disseminate within health services, and can be used by a wide range of clinicians. They are also likely to be cost-effective.

An enhanced therapeutic effect may be obtained through the use of interventions which specifically target the cognitive processes associated with mood disorder within this group. A recent theoretical account of mood disorder [10] suggests that individuals simultaneously hold both positive and negative self-representations. However, depression is associated with heightened access to the negative self-representations, with the relevant pathway being strengthened through regular activation. Korrelboom and colleagues have developed an intervention which consists of a training programme specifically designed to heighten the activation of positive self-representations. The intervention, termed competitive memory training (CoMeT), has been shown to be effective in reducing levels of depression and increasing self-esteem within a range of different disorders [11-15]. Within one study, a mediation analysis suggested that the reduction in depression was mediated by self-esteem [15]. An adapted form of this intervention termed positive memory training (PoMeT) has been developed for use within a U.K. based trial. The PoMeT trial is the first randomised controlled trial to specifically target the treatment of depression in people diagnosed with schizophrenia.

### Hypotheses

The primary hypotheses to be tested is whether within patients who are diagnosed with schizophrenia and exhibit at least a mild level of depression, those who receive positive memory training will demonstrate a higher level of reduction in depressive symptoms than those who receive treatment as usual.

Secondary hypotheses predict that:Positive memory training will reduce the level of distressing psychotic symptoms, as measured by the Psychotic Symptom Rating Scale [16].Positive memory training will be cost-effective.

## Method

The trial is funded by the National Institute of Health Research and received ethical approval for all sites from the Berkshire Research Ethics Committee (REC ref 13/SC/0634). The RCT is conducted by a multidisciplinary team of researchers, clinicians, statisticians and health economists within a number of European institutions and NHS Trusts within the South of England.

## Design

A rater-blind randomised controlled trial using intention to treat comparing positive memory training (PoMeT) and treatment as usual (TAU) with TAU alone. The intervention is to be completed within 3-months from the date of randomisation. Assessments are conducted at baseline, 3-months, 6-months and 9-months from randomisation as shown in Figure 1.

**Figure 1 Fig1:**
[figure not shown]
Flow chart of study design.

The trial is recruiting participants with a diagnosis of schizophrenia or schizoaffective disorder with at least a mild level of depression, defined as a score of 14 or over on the Beck Depression Inventory II [17]. Recruitment to the trial began in May 2014 and is due to be competed in December 2015. Follow-up assessments are due to begin in August 2014 and to end in September 2016.

### Intervention

Positive memory training (PoMeT) is designed to enhance access to positive self-representations resulting in reduced levels of depression and increased self-esteem. It is based on a theoretical account of mood disorder which suggests that positive self representations are relatively dormant within individuals suffering from depression, at least in part due to infrequent activation. The first stage of therapy involves the patient identifying their core negative self-representation, such as being “worthless”. Within the first session the therapist moves towards the identification of personality characteristics which are inconsistent with being “worthless”. Homework involves writing as many specific examples as possible within which the patient has demonstrated these characteristics, e.g. being thanked for being a good friend. Subsequent sessions move towards working with one of these specific ‘positive memories’ in order to maximize the emotional impact. This includes the integrated use of imagery, posture and self-statements whilst ‘reliving’ this past positive event. It is important that the meaning of the positive event provides a direct challenge to the originally identified negative self-representation. A major component of the intervention protocol is daily practise of positive self-representation recall in between the weekly sessions. The final stages of the intervention involves the patient being trained to activate the positive self-representation at a time when an external environmental cue triggers the negative self-representation.

The intervention is manualised and highly structured. Whilst the original protocol adopted 8 sessions of one hour, on the advice of a service-user focus group our study protocol allows up to 12 sessions of one hour within the 3-month treatment period.

The treatment requires therapists to have a core mental health profession and a basic understanding of cognitive behaviour therapy. Within the current trial the intervention is delivered by a nurse who is an accredited cognitive behavioural therapist, a counselling psychologist and a clinical psychologist. Supervision is provided by team members with relevant expertise both in the intervention and patient group. Adherence to protocol is monitored through the use of a measure specifically designed for the current study and aimed to differentiate between the delivery of PoMeT and standard CBT or counselling.

### Treatment as usual (TAU)

Treatment as Usual (TAU) will be provided by the standard in-patient and out-patient services provided by the NHS. This will include neuroleptic medication and the possibility of other psychosocial interventions. All medication and service input received by both the PoMeT + TAU and the TAU groups will be documented during trial assessments.

### Inclusion and exclusion criteria

Potential participants must meet the inclusion criteria of (i) DSM-V diagnosis of schizophrenia of schizoaffective disorder (ii) at least a mild level of depression as measured by scoring 14 or more on the Beck Depression Inventory-II [17] (iii) aged between 18 and 65 (iv) have a sufficient understanding of spoken English to engage with assessments and clinical intervention (v) are able and willing to provide informed consent (vi) do no exhibit an organic impairment which is considered to be the primary diagnosis and (vii) do not exhibit a learning disability.

### Recruitment and randomisation

Recruitment will take place within two UK NHS Trusts, Berkshire Healthcare Foundation Trust and Southern Health Foundation Trust. Eligible participants are identified by trial research assistants, working in collaboration with care coordinators based within community mental health teams. Potentially eligible participants are invited to take part and provide informed consent. Once informed consent has been obtained trained researchers screen patient records to confirm eligibility and administer the Beck Depression Inventory in order to ascertain whether the patient is experiencing at least a mild level of depressed mood. If the patient is eligible the researcher continues with the baseline assessment battery. On completion of assessments the participant is randomised to either the PoMeT + TAU or the TAU group.

Randomisation is stratified by site and severity of depression (above and below a BDI-II score of 29, i.e. a severe level of depression) using randomised-permuted blocks. Group allocation is revealed to the participant, trial manager and trial therapists.

### Measures

#### Primary outcome measure

The primary outcome is current level of depressed mood as assessed by the Beck Depression Inventory- II [17].

#### Secondary outcome measures

Self-esteem is measured using the Roseneberg Self-Esteem Scale [18] which contains ten items measured on a four-point scale. The scale measures state self-esteem by asking the patient to reflect on their current feelings.

Psychotic Symptoms are assessed using two measures. The Positive and Negative Syndrome Scale (PANSS) [19] includes scales of positive symptoms, negative symptoms and general psychopathology and is used widely in schizophrenia research. Also, the Psychotic Symptom Rating Scale (PSYRATS) [16] is used to provide detailed information on the clinical characteristics of hallucinations and delusions, including distress and impact on functioning.

Anxiety is measured using the Generalised Anxiety Disorder Assessment (GAD7) [20] which includes seven items each describing anxiety symptoms, and endorsed on the basis of frequency. Functioning is measured using the Work and Social Adjustment scale [21]. Patient well-being is assessed using the Warwick-Edinburgh Mental Well-being Scale [22], a fourteen-item questionnaire which includes both hedonic and eudaimonic features which are rated on a five-point scale.

A semi-structured interview will be developed in consultation with service-user focus groups to explore the acceptability of the intervention. All participants who are allocated to the Positive Memory Training group will be invited to participate in an interview.

Patients’ health-related quality of life will be measured by the EuroQol EQ-5D [23], a generic, multi-attribute utility scale widely used for economic evaluations. In addition, patients will complete the ICECAP-A [24] and OxCAP-MH [25] instruments , both based on Sen’s capability approach that considers a broad concept of wellbeing including an individual’s ability to ‘do’ and ‘be’ the things that are important in life [26].

Primary informal carers will complete the EuroQol EQ-5D [23] and the Carer Experience Scale [27] via postal questionnaire to measure separately the likely impacts of PoMET on carers’ quality of life and wellbeing.

Costs will be assessed from a broad societal perspective using an amended version of the Client Service Receipt Inventory [28] and therapists’ records. These will include information on all PoMET treatment related costs, other health care resource use costs (including in-patient stays, outpatient visits, community mental health service contacts, primary care contacts, and medications), social care costs, and broader societal impacts (including costs to the patients and their families and lost productivity costs). Costs will be calculated using UK national-level unit costs.

Assessments will be conducted at baseline, 3-months (end of treatment) and at 6-months and 9-months after randomisation. All measures will be completed at baseline, 3-month and 9-month assessment. The 6-month assessment includes only measures of depression, patient health status (including quality of life and wellbeing) and costs.

### Analysis

#### Power

A sample of 50 per group will have 80% power to detect the PoMeT + TAU group presenting with a BDI-II score of 7 or more lower than the TAU group at the 2.5% level of significance (two-tailed).

#### Planned analysis

All analyses will be carried out on an intention to treat principle. Outcome measures for the intervention and treatment as usual (control) groups will be compared using linear mixed-effects models. The dependant variables will be the outcome measures at post-intervention and follow-up. Outcome measures at baseline, group membership and time will be included as fixed explanatory variables. The models will also include random effects for patients to allow for the correlation between post-intervention and follow-up outcome measures. Additionally, the models will contain interaction between time and group to test whether the effects of the intervention and usual treatment vary between post-intervention and follow-up time points. Standard diagnostic evaluations of model assumptions will be conducted to ensure valid inference.

The economic evaluation will be a within trial cost-utility analysis comparing the cost-effectiveness of PoMET in comparison to TAU and will follow the current gold standard methods for economic analyses. Cost-effectiveness will be primarily measured in terms of cost per quality adjusted life year gained (QALY). Alternative analyses will explore the cost-effectiveness of PoMET using capability measures. Uncertainty in the base case results will be assessed using non-parametric methods and extensive sensitivity analyses [29].

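### The listed model terms leave out site, and on the natural reading BDI-II severity in the non-BDI models, although both stratify randomisation; if they are prognostic, standard errors are somewhat too large

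*Protocol article*

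**What the plan says.** Under Recruitment and randomisation, the protocol article states: "Randomisation is stratified by site and severity of depression (above and below a BDI-II score of 29, i.e. a severe level of depression", using permuted blocks. The same section names the sites: "Recruitment will take place within two UK NHS Trusts".

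Under Planned analysis, one linear mixed model is described for all outcome measures. Its fixed effects are given as: "Outcome measures at baseline, group membership and time will be included as fixed explanatory variables". A patient random effect follows, and then: "the models will contain interaction between time and group". Site is named neither as a fixed nor as a random effect. The severity stratum is not named either.

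Under Power, the design figure is: "A sample of 50 per group will have 80% power to detect" a "BDI-II score of 7 or more lower than the TAU group", "at the 2.5% level of significance (two-tailed". No standard deviation is given.

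**The concern.** Stratified blocks force the arms to be nearly balanced within each site and severity level. If those factors predict outcome, the balance reduces the true sampling variability of the treatment estimate. A model without them leaves their variance in the residual or in the patient random effect, so its standard error does not reflect the balance. Intervals are then wider than they need to be and tests reject too rarely.

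The BDI-II model is only partly affected, because the continuous baseline BDI-II largely carries the severity stratum and only site is missing. The models for PSYRATS, PANSS, self-esteem, anxiety, functioning and well-being would contain neither factor if each adjusts for its own baseline alone. At stake is some reported precision in a trial of about 100 participants, not the validity of a positive result.

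**Working it through.** **Inputs.** From Power: 50 per group, 7 BDI-II points, 80% power, two-sided 2.5%. From Recruitment and randomisation: two sites, severity cut at 29, permuted blocks. Assumed, because the article gives no value: R², the share of residual variance (after the baseline outcome) that the omitted stratifiers explain, at 2%, 5% and 10%.

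**Step 1, the plan's own figure.** Without an SD the 80% cannot be reproduced independently. It can only be solved for the SD that makes it true. With critical value 2.241 and power quantile 0.842:

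SD = 7 × √(50/2) / (2.241 + 0.842) = 35 / 3.083 = 11.35

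A noncentral-t calculation gives 11.21. At SD 11.35 the standard error of the difference is 11.35 × √(2/50) = 2.27, and 7/2.27 = 3.083, which returns 80%.

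**Step 2, effect of the omission.** With arms balanced within strata, the true standard error is √(1−R²) times the one that the unadjusted model reports. So:

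- excess in reported SE = 1/√(1−R²) − 1
- actual type I error = 2 × [1 − Φ(2.241/√(1−R²))]
- power without the factors = Φ((3.083 − 2.241)/√(1−R²))
- power with the factors = Φ(3.083/√(1−R²) − 2.241)

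| Assumed R² | SE too large by | Actual type I error | Power without | Power with | Gain (points) |
|---|---|---|---|---|---|
| 0 | 0% | 2.50% | 80.0% | 80.0% | 0 |
| 2% | 1.0% | 2.36% | 80.24% | 80.86% | 0.6 |
| 5% | 2.6% | 2.15% | 80.61% | 82.17% | 1.6 |
| 10% | 5.4% | 1.81% | 81.25% | 84.34% | 3.1 |

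**Step 3, what these R² values mean for site.** For two equal-sized sites the mean difference equals 2 × SD × √R². At SD 11.35 this is 3.2, 5.1 and 7.2 BDI-II points for 2%, 5% and 10%. The 10% row therefore needs a between-Trust gap about as large as the 7-point target effect.

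**Step 4, simulation.** 6,000 trials per setting: N = 100, two sites, blocks of 4 (assumed), one outcome value per patient, and a baseline coefficient of 0.5 on a standardised scale (assumed). Site R² is here a share of total outcome variance. In the BDI-II setting baseline explains 25%, so 5% and 10% of the total are 5/75 = 6.7% and 10/75 = 13.3% of the residual.

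- Mean model SE over true SD of the estimate, without the strata, at site R² of 0, 5% and 10%: 1.00, 1.03 and 1.09 for BDI-II; 1.00, 1.03 and 1.07 for a non-BDI outcome. For BDI-II the formula predicts 1/√(1−0.067) = 1.035 and 1/√(1−0.133) = 1.074.
- With the strata in the model, the ratio in the same settings was 0.99 to 1.01. Monte Carlo error is about 1%, so the 2% setting is too small an effect to resolve in this way.
- The true SD of the BDI-II estimate hardly changed: 0.1591 without and 0.1594 with the strata at site R² 10%. What changed was the mean reported SE: 0.1729 against 0.1615.
- For a non-BDI outcome with no site effect and an assumed additional coefficient of 0.2 on standardised BDI-II, the mean SE was 0.1764 without and 0.1748 with the strata, a ratio of 1.009.

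**The case against.** The strongest objection is that the list of terms need not be closed. The article says that these terms will be included, not that no others will be, and it adds the interaction in a later sentence. An analysis plan that is not shown may add the stratification factors. This stands as a limit: a reader might infer that site was deliberately excluded, and the text does not say so. But the paragraph spells out its terms down to the interaction and the random effect, and a model run as written would ignore site.

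Second, the plural wording about outcome measures at baseline could mean that every baseline measure enters every model. That would cover BDI-II severity. It would not cover site.

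Third, the size depends wholly on an unknown R². A reader might infer that the standard errors are certainly too large, or that severity must be prognostic for psychosis, anxiety and functioning. The article does treat depression as a possible mediator of change in psychotic symptoms, and usual care in two Trusts may differ, so some prognostic value is plausible. Nothing in the article quantifies it beyond each outcome's own baseline. At R² = 0 nothing is lost.

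Fourth, a reader might credit adjustment with the full rise from the stated 80%, for example to 84.3% at R² of 10%. That is the wrong comparator. Under stratified allocation the unadjusted analysis already has 81.3% there, so the gain is about 3 points rather than 4. The 80% also belongs to BDI-II, where only site is missing.

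Finally, the treatment of a score of exactly 29 may be article shorthand for a setting in the randomisation system. It matters only if the stratum itself is used as a covariate.

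**Conclusion.** The point holds in conditional form. The analysis terms as written do not match the stratified design: site is missing from all models, and BDI-II severity is missing from the non-BDI models if each uses only its own baseline. If these factors are prognostic, reported standard errors are somewhat too large and tests conservative. At an assumed R² of 2% to 5% the excess is about 1% to 3% and the power forgone is 0.6 to 1.6 points; at 10% it is 5.4% and 3.1 points.

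These figures rest on near-balance within strata, the normal approximation, the back-solved SD for BDI-II, and one outcome value per patient in place of the full repeated-measures model. The documents do not support reading this as biased estimates, inflated type I error or a less precise estimator: the estimate's true variability is almost unchanged, and what is lost lies in the reported standard error and hence in power. Priority is low to moderate.

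**What to change.** In Planned analysis, add site (two levels) as a fixed effect in all outcome models. In the non-BDI models, also add baseline BDI-II, or the severity stratum exactly as the randomisation system used it. The BDI-II model needs only site, since its continuous baseline already carries severity.

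If the stratum is used, state which level holds a score of exactly 29, consistent with the randomisation system, because the wording above and below 29 places that score in neither.

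The cost is a sentence or two of text and one or two degrees of freedom out of about 100 participants. If the factors prove not to be prognostic, almost nothing is lost.
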